## Abstract

**Background:**

Chronic whiplash is a common and costly problem. Sensory hypersensitivity is a feature of chronic whiplash that is associated with poor responsiveness to physical treatments such as exercise. Modalities such as dry-needling have shown some capacity to modulate sensory hypersensitivity, suggesting that when combined with advice and exercise, such an approach may be more effective in the management of chronic whiplash. The primary aim of this project is to investigate the effectiveness of dry-needling, advice and exercise for chronic whiplash.

**Method/Design:**

A double-blind randomised controlled trial will be conducted. 120 participants with chronic whiplash, grade II will be randomised to receive either 1) dry-needling, advice and exercise or 2) sham dry-needling, advice and exercise. All participants will receive an educational booklet on whiplash. Participants who are randomised to Group 1 will receive 6 treatments of combined dry-needling and exercise delivered in the first 3 weeks of the 6 week program, and 4 treatments of exercise only in the last 3 weeks of the program. Participants randomised to Group 2 will receive an identical protocol, except that a sham dry-needling technique will be used instead of dry-needling. The primary outcome measures are the Neck Disability Index (NDI) and participants' perceived recovery. Outcomes will be measured at 6, 12, 24 and 52 weeks after randomization by an assessor who is blind to the group allocation of the participants. In parallel, an economic analysis will be conducted.

**Discussion:**

This trial will utilise high quality trial methodologies in accordance with CONSORT guidelines. The successful completion of this trial will provide evidence of the effectiveness and cost-effectiveness of a combined treatment approach for the management of chronic whiplash.

**Trial registration:**

ACTRN12609000470291

## Background

Persistent chronic pain following whiplash injury as a result of a motor vehicle crash is a common and costly problem. In Queensland, Australia, the financial costs related to whiplash injury are substantial and exceeded $500 million from 1994-2001 [1]. The maintenance of activity and exercise is recommended for the management of whiplash [2,3]. However, trials of treatment approaches including exercise and activity for chronic whiplash have demonstrated only modest effects on pain and disability levels [4,5]. One reason for these modest effects may be due to the heterogeneous nature of the whiplash condition. Many people with chronic whiplash have a complex clinical presentation with marked sensory disturbance (widespread hyperalgesia, sympathetic nervous system dysfunction) indicative of central nervous system hyperexcitability [6-9]. The presence of these factors is associated with higher levels of pain and disability and poor functional recovery [10,11]. Our data also indicate that patients with these features show a poor response to an exercise-based intervention approach [5].

Modalities such as dry needling and acupuncture are commonly used in the treatment of musculoskeletal pain conditions [12]. With respect to neck pain of all types and not specifically whiplash, a recent systematic review reported moderate evidence for pain relieving effects of these approaches [13]. Furthermore, these modalities can have a modulatory effect on hyperalgesia [14] and they are effective in alleviating symptoms of fibromyalgia [12], a condition that also features characteristics of central hyperexcitability [15]. Together these findings suggest that needling techniques may be effective in the management of chronic whiplash pain, but the use of such interventions in this condition has never been investigated. A recent Cochrane review concluded that dry-needling, added to other conventional therapies such as exercise, is more effective at relieving pain than conventional therapies alone in non-specific low back pain [16]. This combined approach to management has never been investigated in whiplash. Therefore the primary aim of this project is to investigate the effectiveness of dry-needling, advice and exercise compared with sham dry-needling, advice and exercise in chronic whiplash. Effectiveness will be measured by reductions in pain and disability levels and improvements in patients' impressions of overall recovery and quality of life. The secondary aim is to conduct an economic evaluation of the dry-needling, advice and exercise approach.

## Method/Design

### Design

Double-blind randomised controlled trial. Ethics approval has been granted from the Human Research Ethics Committee of the University of Qld (2008002314). Figure 1 shows the flow of participants through the study.

**Figure 1 F1:**
[figure not shown]
**Flow-diagram of trial protocol**.

### Setting

Participants will be assessed at a research laboratory at The University of Queensland. The interventions will be provided at community physiotherapy practices in Brisbane and Ipswich, Queensland.

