### Intervention

All participants will be provided with the patient educational booklet 'Whiplash injury recovery: A self management guide' published by the Motor Accident Insurance Commission (Queensland)[18], which provides information about whiplash, advice on symptom management and illustrates a simple exercise program. Participants will be randomised to one of two groups. Participants in Group 1 will receive 6 treatments of combined dry-needling and exercise delivered in the first 3 weeks of the 6 week program, and 4 treatments of exercise only in the last 3 weeks of the program. Participants in Group 2 will receive an identical protocol, except that a sham dry-needling technique is used instead of dry-needling.

Sham dry-needling uses needles which cause a pricking sensation when pushed against the skin. The needle disappears into the handle with increased pressure. This mechanism invokes a similar sensation to that produced by dry-needling, which includes the non-specific effects of clinician -therapist contact and explanation, as well as the perception that the needle is entering the skin, although sham dry-needling is proposed to have less physiological effect than true needling[19]. Needling sites will be dependent on findings by the physiotherapist following assessment for the presence of hyperalgesia on palpation. Only posterior muscles of the cervical spine and upper thoracic spine will be treated whilst the participant is lying prone, to ensure the participant remains blinded to the needling group allocation. Examples of posterior muscles which may be treated are the trapezius, levator scapulae, splenius capitus, semispinalis and spinalis capitis muscles.

The 6-week exercise program will be carried out under supervision from the physiotherapist and will comprise specific exercises to improve the movement and control of the neck and shoulder girdles (see Table 1). The exercises will be tailored by the physiotherapist for each individual participant, are of a low load nature and are designed to be pain free. At the same time, the physiotherapist will guide the subject's return to normal activities. This programme is similar to those utilised by physiotherapists in clinical practice and has been used in previous studies[5].

**Table 1 T1:** List of Exercises

Exercise	Description

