### Randomisation

Participants will be randomly allocated to groups by concealed allocation. A statistician who is independent of the study will be responsible for generating the computerised randomisation schedule. An independent research assistant will administer the schedule and perform all communication between participants and treating practitioners.

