### Sample size calculations

The NDI was used to determine sample size, as previous clinical trials have shown this variable to have a smaller effect size than the measure of perceived recovery [5]. The minimal clinically important change for the NDI is 7 points [26] with a conservative standard deviation of 18 based on previous work[5,27]. Based on 80% power at *p *= 0.05, 54 participants will be required in each group. Allowing for a 10% loss to follow up, a total of 60 participants will be required in each group, with 120 participants in total.

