### Data management and analysis

All analyses will be conducted on an intention to treat basis. The outcomes measured at 6, 12, 24 and 52 weeks will be analysed using linear mixed and logistic regression models that will include their respective baseline scores as a covariate, subjects as a random effect and treatment conditions as fixed factors. Age, gender, duration of condition and IES scores will be included as covariates in the analysis. Regression diagnostics will be used to check for normality of the measures and homogeneity of variance as appropriate. Alpha will be set at 0.01.

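### Physiotherapists at several community practices deliver operator-dependent treatment, but the stated model has no practice or therapist term

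*Protocol article*

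**What the plan says.** Under Setting, the protocol article places treatment at more than one site in two cities: "The interventions will be provided at community physiotherapy practices in Brisbane and Ipswich, Queensland". It gives no number of practices or therapists.

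Under Intervention, both the tested component and the co-intervention depend on the operator's judgement. On needling: "Needling sites will be dependent on findings by the physiotherapist following assessment for the presence of hyperalgesia on palpation". On exercise: "The exercises will be tailored by the physiotherapist for each individual participant". The physiotherapist also guides the return to normal activity.

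Under Randomisation, the unit is the individual: "Participants will be randomly allocated to groups by concealed allocation". The section does not say how practices or therapists relate to the arms.

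Under Data management and analysis, the model is spelled out. It includes "respective baseline scores as a covariate, subjects as a random effect and treatment conditions as fixed factors", and then: "Age, gender, duration of condition and IES scores will be included as covariates in the analysis". The only grouping term is the subject. The sample size section makes no allowance for clustering.

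**The concern.** Participants treated by the same physiotherapist may have more similar outcomes than participants treated by different ones. A model whose only random effect is the subject puts this shared component into between-subject variance and treats participants as independent of one another. How much that matters depends on how practices relate to the arms:

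- **Each practice treats both arms, and practices differ only in general level.** Precision is lost that a practice term would recover.
- **A therapist or practice delivers only one arm.** Operator differences add to the variance of the treatment contrast, and the model's standard error does not reflect this.
- **Both arms in each practice, but the needling effect differs between practices.** The standard error is too small for a conclusion about community practices in general, and the stated analysis would not show whether an effect came from one or two operators.

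The article lists its model terms one by one. The point therefore concerns a stated model, not detail left to another document.

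**Working it through.** **Inputs from the protocol article.** NDI target difference 7 points, SD 18, 54 per group before loss and 60 per group randomised (Sample size calculations); analysis alpha 0.01 (Data management and analysis).

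**Assumed, because the article does not give them.** 4 to 10 practices of equal size; ICC 0.01 to 0.10, meaning practice's share of a total variance of 18² = 324; a between-practice SD of the needling effect of 3 to 5 points. Repeated visits and covariates are ignored.

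**The plan's own figure.** The plan gives no figure for clustering. Its sample size does not follow from its inputs: 2 × (1.960 + 0.842)² × 324 / 49 = 103.8, or 104 per group two-sided (82 one-sided), against the stated 54. The loss step does reproduce: 54 / 0.9 = 60. That is a separate issue. Below, 54 and 60 serve only as the planned numbers.

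**Case 1: both arms in every practice, level differences only.**
- Unadjusted SE with 60 per arm: √(2 × 324 / 60) = √10.8 = 3.29.
- Part of that variance due to practice: ICC × 10.8 = 0.54 at ICC 0.05 and 1.08 at ICC 0.10. This lies inside the 10.8; it does not add to it.
- SE with a practice term: √(10.8 − 0.54) = 3.20, or √(10.8 − 1.08) = 3.12.
- Reduction: 1 − √0.95 = 2.5%, or 1 − √0.90 = 5.1%.
- Power for 7 points at two-sided 0.05 with 54 per arm: 0.524 without the term; 0.528 (ICC 0.01) to 0.545 (ICC 0.05) with it. The gain is 0.4 to 2 percentage points.
- Simulation of an analysis that ignores practice (4,000 runs per setting; 4, 6 or 10 practices; ICC 0.02 or 0.05): no bias beyond simulation error, and type I error 0.043 to 0.053 at nominal 0.05.

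**Case 2: each practice or therapist delivers one arm only.** Design effect D = 1 + (m − 1) × ICC, with 108 completers; actual size = 2 × [1 − Φ(z / √D)].

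| Practices (m) | ICC | D | Effective n per arm (54 / D) | Size at nominal 5% | Size at nominal 1% |
|---|---|---|---|---|---|
| 10 (10.8) | 0.01 | 1.10 | 49.2 | 6.1% | 1.4% |
| 10 (10.8) | 0.05 | 1.49 | 36.2 | 10.8% | 3.5% |
| 4 (27) | 0.01 | 1.26 | 42.9 | 8.1% | 2.2% |
| 4 (27) | 0.05 | 2.30 | 23.5 | 19.6% | 8.9% |

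**Case 3: both arms in every practice, needling effect varying with SD t across 8 practices.** True SE = √(10.8 + t² / 8).
- t = 3: √11.925 = 3.45; ratio 3.29 / 3.45 = 0.952; actual size 6.2% at nominal 5% and 1.4% at nominal 1%.
- t = 5: √13.925 = 3.73; ratio 0.881; actual size 8.4% and 2.3%.
- A simulation with 4 to 10 practices and an effect SD of 2 × 18 × √0.02 = 5.1 points gave about 7 to 12% at nominal 5%.

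These sizes refer to a null in which the mean effect over a wider population of practices is zero while individual practices differ. If needling has no effect anywhere, t = 0 and the inflation disappears.

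**The case against.** The strongest reply is that individual, concealed randomisation already protects the comparison. A reader might infer that one practice delivering mostly real needling and another mostly sham would turn operator skill into an apparent treatment effect. The documents do not support reading this as bias. Chance imbalance between practices is sampling error and is already covered by the 3.29 standard error. For the same reason, sharing a physiotherapist does not by itself invalidate the test when practices are crossed with arm. This part of the reply stands in full.

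A reader might also infer that allocation is simple and unstratified. The article says only that an independent statistician generates a computerised schedule. A condensed article may leave out blocking and stratification, so its silence shows nothing, and the point does not rest on it.

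The treatment is also partly standardised: a fixed number of sessions, posterior muscles only, participants prone, and a common exercise list, with tailoring in both arms. Differences between practices are therefore plausible but not established.

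Finally, the inflation in Case 3 depends on an assumed spread of effects, and a practice intercept would not cure it. That is correct, and it is why the intercept alone is not enough. What the reply does not remove is the omission from an explicitly listed model, and the open question of how therapists relate to arms.

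**Conclusion.** The point holds as a modest, inexpensive improvement to a stated model. It does not show that the treatment comparison is biased. If both arms are treated in every practice and practices differ only in level, the gain from a practice term is about 3 to 5% of the standard error at an assumed ICC of 0.05 to 0.10, or 0.4 to 2 points of power at ICC 0.01 to 0.05.

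The standard error is too small only under one of two conditions that the article neither states nor excludes. If therapists are tied to one arm, actual size would be about 6 to 20% at nominal 5%, for 4 to 10 practices and ICC 0.01 to 0.05. If the needling effect varies by practice and the conclusion is meant to generalise beyond the participating practices, size would be 6.2 to 8.4% at nominal 5%, and 1.4 to 2.3% at the planned alpha of 0.01, for 8 practices and an effect SD of 3 to 5 points. The number of practices, the ICC and the effect SD are all assumptions.

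**What to change.** - Add treating practice (or therapist) to the model under Data management and analysis, as a random intercept, or as a fixed effect if there are few.
- As a sensitivity analysis, fit a random treatment-by-practice effect and report the treatment effect by practice. This addresses variation in the needling effect, which the intercept does not.
- State how practices and therapists relate to the arms, and confirm that each practice treats both. If any delivers one arm only, a fixed practice effect cannot separate practice from treatment there, and the clustering must be carried into the standard error and the sample size.

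The cost is a few degrees of freedom and a rule, set in advance, for pooling very small practices. With few practices the treatment-by-practice variance will be poorly estimated, so that analysis should stay supportive. The model changes can be made at any time before unblinding.

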### Participants

A total of 120 participants with chronic whiplash will be recruited. Inclusion criteria are Whiplash Grade II (no fracture or dislocation and no clinical neurological deficit on clinical examination) [17] of at least 3 months but less than 2 years in duration; moderate pain and disability (Neck Disability Index minimum of 28/100); and presence of sensory hypersensitivity, defined as 2 out of a possible 3 of the following: cold pain threshold (> 15°C, males and females), pressure pain thresholds over the cervical spine (females < 185 kPa, Males < 210 kPa), and pressure pain thresholds over the median nerve (females < 210 kPa, Males < 250 kPa) *(6)*. Participants must also be naive to dry-needling and acupuncture techniques and must not be receiving any other treatment for their whiplash symptoms at the time of recruitment. Exclusion criteria are known or suspected serious spinal pathology (e.g. metastatic, inflammatory or infective diseases of the spine); spinal surgery in the past 12 months; diagnosis with a mental health condition; confirmed fracture or dislocation at time of injury (Whiplash Grade IV); and nerve root compromise defined as at least 2 of the following signs: weakness, reflex changes, or sensory loss (Whiplash Grade III)[17]. Participants will be recruited from local medical practices and via electronic and print media advertising.

### Intervention

All participants will be provided with the patient educational booklet 'Whiplash injury recovery: A self management guide' published by the Motor Accident Insurance Commission (Queensland)[18], which provides information about whiplash, advice on symptom management and illustrates a simple exercise program. Participants will be randomised to one of two groups. Participants in Group 1 will receive 6 treatments of combined dry-needling and exercise delivered in the first 3 weeks of the 6 week program, and 4 treatments of exercise only in the last 3 weeks of the program. Participants in Group 2 will receive an identical protocol, except that a sham dry-needling technique is used instead of dry-needling.

Sham dry-needling uses needles which cause a pricking sensation when pushed against the skin. The needle disappears into the handle with increased pressure. This mechanism invokes a similar sensation to that produced by dry-needling, which includes the non-specific effects of clinician -therapist contact and explanation, as well as the perception that the needle is entering the skin, although sham dry-needling is proposed to have less physiological effect than true needling[19]. Needling sites will be dependent on findings by the physiotherapist following assessment for the presence of hyperalgesia on palpation. Only posterior muscles of the cervical spine and upper thoracic spine will be treated whilst the participant is lying prone, to ensure the participant remains blinded to the needling group allocation. Examples of posterior muscles which may be treated are the trapezius, levator scapulae, splenius capitus, semispinalis and spinalis capitis muscles.

The 6-week exercise program will be carried out under supervision from the physiotherapist and will comprise specific exercises to improve the movement and control of the neck and shoulder girdles (see Table 1). The exercises will be tailored by the physiotherapist for each individual participant, are of a low load nature and are designed to be pain free. At the same time, the physiotherapist will guide the subject's return to normal activities. This programme is similar to those utilised by physiotherapists in clinical practice and has been used in previous studies[5].

**Table 1 T1:** List of Exercises

Exercise	Description
1. Flexors of the cranio-cervical spine	Re-education of cranio-cervical flexion movement Training holding capacity of the neck flexors Retraining eccentric control of the cranio-cervical flexors in upright postures

2. Extensors of the cranio-cervical spine	Re-education of cranio-cervical extension movement Training holding capacity of the neck extensors

3. Re-education of neutral posture	Re-education of neutral spine in sitting, including lumbo-pelvic, thoracic and cervical spine neutral Progression to other functional postures (patient specific)

4. Retraining of the scapular muscles	Retraining scapular orientation in neutral posture Training endurance capacity of the scapular stabilizers Retraining dynamic scapular control with arm movement and load

5. Co-contraction of the neck flexors and extensors	Facilitated with rotation, using self-resisted isometric rotation in either supine, or in correct upright sitting posture

6. Strength training of the flexor synergy	Head lift in supine, preceded with cranio-cervical flexion followed by cervical flexion to just lift the head from the supporting surface. Graded reduction in pillow height to flat surface

### Outcome Measures

Age, gender, time since injury, compensation status, previous treatments and medication usage for the whiplash condition will be obtained at baseline. The assessor administering the outcomes will be blind to the group allocation of the participant. Outcome measures will be assessed at baseline, 6, 12, 24 and 52 weeks after randomization.

### Primary outcome measures

1. Neck-specific measure of disability (Neck Disability Index)[20]

2. Patient's global impression of recovery (-5 to +5 scale) [21]

### Secondary outcome measures

3. Average pain intensity over last week (Visual Analogue Scale)[21]

4. Average pain intensity over last 24 hours (Visual Analogue Scale)[21]

5. Patient-generated measure of disability (Patient-Specific Functional Scale)[22]

6. Whiplash-specific measure of disability (Whiplash Disability Questionnaire) [23]

7. Generic measure of health status (SF-36) [24]

8. Measures of physical impairment (Cervical range of movement, pressure pain threshold, cold pain threshold) [25]

9. Impact of events scale (IES) [25]

10. Pain Catastrophising Scale (PCS)

11. Posttraumatic stress Diagnostic Scale (PDS)

12. Self report Leeds Assessment of Neuropathic Symptoms and Sign (S-LANSS Pain Score)[25]

### Adverse Events

All adverse effects, defined as any negative or unwanted reactions to the interventions will be recorded. These will include increased pain (greater than 2 points the VAS scale for greater than 1 week), skin infection, skin irritation or any other reported physical discomfort. An adverse effects committee (chaired by MS) will manage any adverse reactions as they occur. Adverse effects of treatment will be identified using open-ended questioning at the 6 week follow-up assessment.

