## Discussion

Although many people experience rapid recovery from pain and disability associated with whiplash within the first three months, a significant proportion can have ongoing mild to moderate pain and disability[28]. It has been shown that the presence of widespread sensory hypersensitivity indicative of augmented pain processing mechanisms is associated with higher levels of pain, disability and poor functional recovery following whiplash injury [29]. Chronic patients with these features have been shown to have a poor response to an exercise-based intervention approach[5]. In order to enhance the treatment outcomes of an exercise intervention, an additional modality or technique could be used in conjunction with an exercise programme to address the sensory hypersensitivity of whiplash. Modalities such as dry needling and acupuncture are commonly used in the treatment of musculoskeletal pain conditions[12], although the benefit of dry needling for the treatment of whiplash is not yet known. Therefore, this trial aims to investigate whether the addition of dry needling to an exercise programme will reduce pain and disability of chronic whiplash.

The exercise programme received by all participants in the trial includes specific exercises to re-educate cervical and scapular muscle control endurance and strength and are of low-load in nature. These exercises are tailored to the ability of the participants by the trial physiotherapists. This type of exercise programme has previously shown modest effects in the treatment of chronic whiplash by reducing pain and disability [4,5] and was therefore the programme of choice for this trial.

A sham dry needling intervention will be used as a in the comparison group to assess the effects of dry-needling on whiplash. Sham dry needling invokes a similar sensation to that produced by true dry-needling, without the needle entering the skin. This technique is proposed to have a lesser physiological effect than true needling [19]. Application of the sham and true dry needles are to the posterior cervical and thoracic spine whilst the participant is prone, which will allow participant blinding to their group allocation. A blinded independent trial assessor will conduct participant assessments. The methodology of this double-blind randomised controlled trial meets the CONSORT statement and guidelines [30].

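### Adverse effects are recorded only as reactions to treatment, so events nobody links to treatment can be lost and a true difference in harms between real and sham needling diluted

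*Protocol article*

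**What the plan says.** The Adverse Events section of the protocol article fixes the recorded item: "All adverse effects, defined as any negative or unwanted reactions to the interventions will be recorded". It then gives examples: "These will include increased pain (greater than 2 points the VAS scale for greater than 1 week), skin infection, skin irritation or any other reported". The last item on that list, cut short here, is a broad one for further bodily complaints. The section names one way of finding adverse effects: "Adverse effects of treatment will be identified using open-ended questioning at the 6 week follow-up assessment". A committee "will manage any adverse reactions as they occur". The section names nobody who decides whether an event is a reaction.

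Two other parts of the article matter here. On the control, the Intervention section says "Participants in Group 2 will receive an identical protocol, except that a sham dry-needling technique is used instead of dry-needling", and the Discussion adds "Sham dry needling invokes a similar sensation to that produced by true dry-needling, without the needle entering the skin". On blinding, the Outcome Measures section says "The assessor administering the outcomes will be blind to the group allocation of the participant", and the Intervention section has needling done with the participant prone so that participants stay unaware of their group.

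**The concern.** A randomised comparison against sham can show harm from needling by counting all events in each group. No one then has to decide, case by case, what caused an event. The article instead puts that decision ahead of the record. In one participant it is a hard decision: everyone enrolled has chronic neck pain and everyone exercises, so a new complaint could come from the needle, the exercise or the condition.

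What is at stake is the completeness of the harms record. An event that was never written down cannot be recovered by any later analysis, and a harm not yet recognised as an effect of needling is the kind most likely to be missed.

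**Working it through.** **1. Is the causal condition really in the text?** The definition sentence speaks of reactions to the interventions, and the detection sentence speaks of effects of treatment. The list of examples opens by referring back to those adverse effects, so each item, including the broad last one, falls under the causal definition. The section heading speaks of events, but no sentence in the article provides for recording events regardless of cause. The condition is stated; it is not a detail left open.

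**2. Who applies it, and do they know the group?** The only stated detection route is questioning at the 6-week assessment. Participants are meant to be blinded and the outcome assessor is blind. On that route there is no documented reason for attribution to differ between groups. The physiotherapist who applies the needle can hardly be blind, since one needle enters the skin and the other does not. Unequal attribution is therefore possible for reactions first noted in the clinic, but no sentence says that the physiotherapist records events or decides their cause.

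**3. Which events are exposed?** The outcome sections schedule the Neck Disability Index, pain scales, the Whiplash Disability Questionnaire, SF-36, range of movement and pain thresholds for both groups at baseline and at 6, 12, 24 and 52 weeks. Worsening of pain or disability at these visits is measured without attribution. What remains exposed is mainly skin events, other complaints and medical events outside those scales.

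**4. What does equal filtering do?** The article states no event rate and no harms test, so there is no figure to reproduce. The following is illustration only.

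Inputs: n = 60 per group (Sample size calculations: "Allowing for a 10% loss to follow up, a total of 60 participants will be required in each group, with 120 participants in total"). Assumed: true proportions with an event p1 = 40% (real) and p2 = 20% (sham), a share q of these attributed to treatment and so recorded, the same q in both groups, and a two-sided 5% test.

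Recorded proportions are q·p1 and q·p2. The recorded difference is q(p1 − p2), while the ratio p1/p2 is unchanged.

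Counts: 60 × 0.40 = 24 and 60 × 0.20 = 12 participants with an event, 36 in all. At q = 0.5 the record holds 12 and 6, so 18 of 36 are lost.

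Power = Φ{[d√n − 1.96√(2m(1 − m))] / √(r1(1 − r1) + r2(1 − r2))}, where r1 and r2 are the recorded proportions, d their difference and m their mean.

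- q = 1: (0.20√60 − 1.96√0.42)/√0.40 = (1.549 − 1.270)/0.632 = 0.441, power 67%.
- q = 0.5: (0.10√60 − 1.96√0.255)/√0.25 = (0.775 − 0.990)/0.5 = −0.430, power 33%.

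| q | Recorded difference (points) | Power |
|---|---|---|
| 1 | 20 | 67% |
| 0.75 | 15 | 50% |
| 0.5 | 10 | 33% |
| 0.25 | 5 | 18% |

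Range over other assumed rates, moving from q = 1 to q = 0.5: with 30% against 15%, power goes from 50% to 25%; with 50% against 25%, from 82% to 42%.

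**5. What can the sham contrast replace?** The groups differ only in the needle. Comparing all events by group can show harm from needling without attribution. It cannot show harm from exercise or advice, which both groups receive.

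**The case against.** The strongest reply is that the filter is weaker than the definition suggests. The section names no judge and no exclusion step, and its last example is broad enough that many complaints would be recorded in practice. This stands in part: it is too strong to say that unattributed events never enter the data. But the broad item sits inside the causal definition, and if it was meant to override that definition, the section can be read in two ways and needs rewording anyway.

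A second reply is that pain and disability are already measured in both groups, and that some attribution is needed for harms of exercise. Both points stand. They narrow the exposure and give a relatedness judgement a proper use, but they do not justify making it the condition for recording.

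A third reply is that a condensed article leaves harms forms and analysis to the full protocol. That is fair for the form layout and the analysis, and the article indeed describes no between-group comparison of harms. It does not cover a definition that the article itself fixes.

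A reader might go further and infer that treating physiotherapists, knowing the group, would call complaints reactions more readily after real needling, so that the record overstates its harm. The documents do not support this. They do not give the physiotherapist that role, and they offer no attribution rates. An unblinded therapist could also err the other way and be slow to blame the real needle. Neither direction nor size can be derived.

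**Conclusion.** The point holds in a limited form. The article makes attribution to treatment a condition of recording, which loses events and, with attribution equal in both groups, shrinks any true difference in harms in proportion to the share attributed. The power figures rest wholly on assumed event rates, an assumed attribution share and an assumed two-sided 5% test; only the group size comes from the article. Bias between groups is possible only for reactions noted in the clinic by staff who know the allocation, and its direction and size are unknown. The exposure lies mainly outside pain and disability. Nothing here touches the primary efficacy analysis. This is a cheap improvement, not a fault that threatens the trial.

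**What to change.** In the Adverse Events section, define the recorded item as any new or worsened symptom or medical event from randomisation, whether or not it is thought related to treatment, and ask about it in the same way in both groups. Keep presumed relatedness (needling, exercise, other) as a separate field, judged without knowledge of group. Report all events by group, with those judged related as a secondary summary.

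The cost is a change of wording and one extra field on the form. More background whiplash symptoms will be recorded and must be handled. Nothing now collected is lost, and no treatment rule changes. The change has to be in place before data collection, because unrecorded events cannot be restored afterwards.
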